### Interventions

Patients will be randomly allocated to either combined ESWL and endoscopic treatment or sham treatment.

#### Combined ESWL and endoscopic treatment

Patients enrolled in the active treatment group will be subjected to ESWL followed by ERCP. In India, patients with CP typically present with large pancreatic stones that tend to be dense and spiculated. In order to ensure complete stone clearance, ESWL and ERCP are therefore performed together and in agreement with clinical practice in most centers [10, 31].

ESWL will be conducted with the patient under epidural anesthesia. For epidural anesthesia, bupivacaine will be used to block the T6–T12 thoracic spinal segments. The patient’s eyes will be lightly covered during the procedure. Once epidural anesthesia is achieved, the patient will be given a light sedation, and ESWL will be performed using a third-generation Dornier dual focus lithotripsy system (Dornier Delta 3; Dornier MedTech GmbH, Weßling, Germany), providing a maximum of 5000 shocks at the rate of 90 shocks per minute. If complete stone clearance is not achieved during the first ESWL session, a second session will be scheduled the following day.

After lithotripsy, stone fragments will be removed during an ERCP procedure. An endoscopic pancreatic sphincterotomy will be performed, and complete stone removal will be attempted with registration of pancreatic duct clearance. If cannulation fails after a maximum of five attempts, the patient will be subjected to precut sphincterotomy. In case a pancreatic duct stricture is identified during the ERCP procedure that was not detected by MRCP prior to enrollment, the stricture is dilated and followed by pancreatic stent insertion. A pancreatic duct stent will also be inserted in case of incomplete stone removal during the ERCP procedure.

Patients undergoing pancreatic duct stenting will be referred for a new ERCP procedure after 6 months for stent exchange or removal (after completion of all study assessments). When complete runoff of contrast material is observed after removal of the stent and an extraction balloon can be passed through the pancreatic duct, endoscopic treatment is considered completed, and further stenting will be stopped. Persistent strictures will be treated by repeated endoscopic dilations and sequential insertion of new stents in agreement with the European Society of Gastrointestinal Endoscopy guidelines [32].

#### Sham treatment

In the sham/control group, patients will be given a transient superficial pinprick sensation to give the feeling of epidural anesthesia prior to sham ESWL. Subsequently, the lithotripsy machine will be switched on, without establishing any form of contact with the patient’s body. The patient’s eyes will be lightly covered during the entire procedure. Following sham ESWL, patients will be subjected to sham ERCP with duodenal intubation of the endoscope and examination of the papillary area, but no pancreatic ductal intervention will be performed.

#### Concomitant medication

Patients will be instructed not to change their regular pain treatment during the trial period. Regular pain treatment will be recorded twice: at the screening visit and at the last visit. Rescue pain medication, taken on an “as needed basis,” is allowed throughout the trial period, and its use will be documented and quantified in the pain diary. Patients with exocrine pancreatic insufficiency will remain on enzyme replacement therapy during the trial period and follow-up.

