#### Primary clinical endpoint

The primary clinical endpoint is pain relief. Average and maximal daily clinical pain intensity scores will be recorded in a patient pain diary based on a 0–10 VAS, with registration of the baseline pain intensity scores done in the week prior to intervention and weekly recordings continued for a 3-month period after intervention. Mean values of pain scores will be calculated over 1 week to adjust for day-to-day variability in pain intensity. The difference in pain scores between patients receiving active treatment (ESWL and ERCP) and sham treatment are compared, with the primary comparison of average pain scores 3 months after intervention. Weekly telephone interviews from a study coordinator will be undertaken to facilitate accurate registration and compliance pain score.

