#### Secondary clinical endpoints

Difference between groups in pain scores after 6 months.The ratio of responders versus nonresponders defined by a decrease in the average clinical pain score (VAS) of 30% after 3 and 6 months compared with baseline.Difference between groups in number of pain-free days after 3 and 6 months.Change in analgesic consumption (if used) after 3 and 6 months compared with baseline.Difference between groups in total number of hospitalizations during the study period.Difference between groups in total duration of hospital stays during the study period.Difference in total loss of working days due to CP between groups during the study period.Difference between groups in cumulative cost attributed to CP-related treatment and disability (loss of working days) during the study period.Difference between groups in quality of life using the European Organization for Research and Treatment of Cancer Quality of Life questionnaire after 3 and 6 months [15].Difference between groups in pain and physical functioning composite scores of the modified Brief Pain Inventory–short form after 3 and 6 months [16].Difference between groups in depression and anxiety scores of the Hospital Anxiety and Depression Scale after 3 and 6 months [33].Patient global impression of change after 3 and 6 months [18].Assessment of complications resulting from interventions during the study period.

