**Fig. 1 Fig1:**
[figure not shown]
Schedule of enrollment, interventions, and assessments. ^a^Baseline variables: age; sex; etiology and duration of chronic pancreatitis (CP); history of acute pancreatitis; current alcohol and smoking status; complications of CP, including exocrine pancreatic insuficiency (EPI) and diabetes mellitus; cross-sectional imaging results; medications, including analgesics; and past history of endoscopic and/or surgical treatment. ^b^Primary outcome: Pain scores documented in a weekly pain diary based on a 0–10 visual analogue scale. ^c^Secondary outcomes: Pain scores after 6 months, > 30% pain relief, number of pain-free days, analgesic consumption, frequency of hospitalizations, quality of life (European Organization for Research and Treatment of Cancer Quality of Life questionnaire), pain and physical functioning composite scores (modified Brief Pain Inventory–short form), anxiety and depression scores, patient global impression of change, and complications. ^d^Quantitative sensory testing assessment parameters. *ERCP* Endoscopic retrograde cholangiopancreatography, *ESWL* Extracorporeal shock wave lithotripsy

The follow-up duration is 6 months from randomization with scheduled visits after 3 months (primary study period) and 6 months (follow-up). The questionnaires and pain diary used for collection of clinical endpoints are described in the previous sections on primary and secondary clinical endpoints. In addition, QST profiles will be recorded prior to intervention as well as 24–48 h after and 3 months after intervention. A schedule for the study assessment parameters is provided in Fig. 1.

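### Regular analgesic use is recorded at two time points, but the analgesic endpoint needs three; the record most likely missing is month 3, the primary time point

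*Protocol article*

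**What the plan says.** All the relevant statements are in the protocol article.

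- **Concomitant medication**, on regular treatment: "Patients will be instructed not to change their regular pain treatment during the trial period", and "Regular pain treatment will be recorded twice: at the screening visit and at the last visit".
- **Concomitant medication**, on rescue medication: it "is allowed throughout the trial period, and its use will be documented and quantified in the pain diary".
- **Secondary clinical endpoints**: "Change in analgesic consumption (if used) after 3 and 6 months compared with baseline".
- **Outcome measures** (text following the Fig. 1 legend): follow-up lasts 6 months from randomization, with "scheduled visits after 3 months (primary study period) and 6 months (follow-up)". The same section lists analgesics among the medications registered at baseline.
- **Primary clinical endpoint**, on the diary: pain scores are registered in the week before intervention, with "weekly recordings continued for a 3-month period after intervention".

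**The concern.** The recording rule and the endpoint do not fit together. The rule fixes the number of recordings of regular treatment at two and says when they occur. The endpoint asks for a change from baseline at two later times. This is not detail left to an analysis plan, because an analysis plan cannot recover data that the protocol says are collected at other times.

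Two things are at stake. First, a named secondary endpoint lacks its data on regular analgesics at one of its two time points. Second, the missing time point is most likely month 3, when the primary comparison of pain scores is made. Pain scores and analgesic use are linked. If sham patients raised their regular analgesics by month 3 despite the instruction, or actively treated patients lowered theirs, the pain difference would narrow. No record of regular use at month 3 would be available to check this. The Statistical analysis section keeps all randomized patients regardless of adherence, so patients who changed their analgesics remain in the comparison.

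**Working it through.** The plan gives no figure for this endpoint, so the check is to set the sections side by side and count.

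**Step 1. Time points needed and supplied for regular treatment.** Needed: baseline, month 3, month 6, which is 3. Supplied: screening and last visit, which is 2. Shortfall: 3 − 2 = 1. The separate baseline registration of medications adds nothing after randomization and does not reduce the shortfall.

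**Step 2. Which time point is missing.** The last scheduled visit is month 6, so the natural reading leaves month 3 empty. The alternative reading puts the last visit at month 3. It has some footing because the Concomitant medication section names the trial period and the follow-up as separate things (patients with exocrine insufficiency "will remain on enzyme replacement therapy during the trial period and follow-up"), and Outcome measures labels month 6 as follow-up. On that reading month 6 is empty.

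**Step 3. Rescue use.** It is recorded in the diary. The 3-month duration is stated under the primary endpoint, for pain scores. Two other secondary endpoints, pain scores and pain-free days, also extend to month 6. They imply some recording after month 3, but no text describes it. Both diary lengths are therefore carried forward.

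**Step 4. What is available under each reading.**

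| Last visit | Diary runs to | Month 3: regular / rescue | Month 6: regular / rescue | Both components available at |
|---|---|---|---|---|
| Month 6 | Month 3 | no / yes | yes / no | neither time |
| Month 6 | Month 6 | no / yes | yes / yes | month 6 only |
| Month 3 | Month 3 | yes / yes | no / no | month 3 only |
| Month 3 | Month 6 | yes / yes | no / yes | month 3 only |

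In all four rows, at least one of the two time points lacks regular use. Both time points are incomplete only in the first row, and only if consumption means regular plus rescue use combined.

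**Step 5. Reach into the rest of the plan.** The sample size does not use analgesic data: 2 × (1.960 + 1.282)² × (45/30)² = 47.3, rounded up to the stated 48 per group. The primary mixed model has terms for treatment, week and their interaction, and none for analgesics. Neither is affected.

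**The case against.** A reader might infer that the change in analgesic consumption cannot be computed at month 3 or at month 6. The documents do not support that. The endpoint is not defined as regular plus rescue use combined. With the last visit at month 6, change in regular use at month 6 and rescue use at month 3 can both be obtained. The 3-month diary limit is written for pain scores, and the 6-month pain endpoints point to later recording. Failure at both times is one of four readings.

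It can also be said that Fig. 1, which holds the assessment schedule, is not shown. Its legend lists analgesic consumption among the secondary outcomes, and it may show collection at both visits. That limits how firmly one can say the data will not exist. It does not remove the contradiction, because the text would still state two recordings.

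A third argument is that regular treatment is meant to stay constant, and that rescue medication, the permitted route to extra analgesia, is captured during the primary period. This has some weight: a lasting increase in regular treatment would also appear at a month-6 visit. But an instruction is not a measurement, the endpoint exists to measure change, and a month-6 record does not show what was taken at month 3.

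Finally, a reader might infer that the primary result is biased. No size of bias can be derived from the documents. What is lost is the ability to check, not the validity of the primary analysis.

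**Conclusion.** The contradiction stands: under every reading, two recordings of regular treatment cannot serve an endpoint at baseline, month 3 and month 6. Taking the last visit as month 6, which the visit schedule supports, the gap falls at month 3. The 3-month pain comparison then cannot be read against regular analgesic use at that time in any of the 106 planned patients. The month-6 source of rescue use is unclear, not shown to be missing.

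The severity is moderate. One of the thirteen listed secondary endpoints is affected directly, and interpretation of the primary result is affected indirectly. The conclusion assumes that the article's sentence on recordings reflects actual practice; the schedule in Fig. 1 could not be checked.

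**What to change.** Amend the Concomitant medication section so that regular pain treatment is recorded at screening, at the 3-month visit and at the 6-month visit. State that rescue use is also captured for the 6-month assessment, for example through one diary week before that visit. Check that Fig. 1 and the Concomitant medication, Primary clinical endpoint and Secondary clinical endpoints sections then agree. How regular and rescue use are combined, and how non-users are handled, can be left to the analysis plan.

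The cost is one more medication entry at a visit that already takes place, and a short extra diary period. No new visit or procedure is needed. Timing matters: the Trial status section puts the first randomization at January 4, 2020, so the first 3-month visits fall around early April 2020. For patients already past month 3 when the change takes effect, regular use at that time could be recovered only by recall, and such entries should be marked as recalled.

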### Outcomes

The study consists of a clinical part and an experimental part. The clinical part of the study aims to investigate the pain-relieving effects of combined ESWL and endoscopic treatment in patients with painful CP in comparison with sham treatment. The experimental part of the study aims to evaluate if QST profiles obtained prior to ESWL and endoscopic intervention can be used for prediction of treatment outcome.

#### Primary clinical endpoint

The primary clinical endpoint is pain relief. Average and maximal daily clinical pain intensity scores will be recorded in a patient pain diary based on a 0–10 VAS, with registration of the baseline pain intensity scores done in the week prior to intervention and weekly recordings continued for a 3-month period after intervention. Mean values of pain scores will be calculated over 1 week to adjust for day-to-day variability in pain intensity. The difference in pain scores between patients receiving active treatment (ESWL and ERCP) and sham treatment are compared, with the primary comparison of average pain scores 3 months after intervention. Weekly telephone interviews from a study coordinator will be undertaken to facilitate accurate registration and compliance pain score.

#### Secondary clinical endpoints

Difference between groups in pain scores after 6 months.The ratio of responders versus nonresponders defined by a decrease in the average clinical pain score (VAS) of 30% after 3 and 6 months compared with baseline.Difference between groups in number of pain-free days after 3 and 6 months.Change in analgesic consumption (if used) after 3 and 6 months compared with baseline.Difference between groups in total number of hospitalizations during the study period.Difference between groups in total duration of hospital stays during the study period.Difference in total loss of working days due to CP between groups during the study period.Difference between groups in cumulative cost attributed to CP-related treatment and disability (loss of working days) during the study period.Difference between groups in quality of life using the European Organization for Research and Treatment of Cancer Quality of Life questionnaire after 3 and 6 months [15].Difference between groups in pain and physical functioning composite scores of the modified Brief Pain Inventory–short form after 3 and 6 months [16].Difference between groups in depression and anxiety scores of the Hospital Anxiety and Depression Scale after 3 and 6 months [33].Patient global impression of change after 3 and 6 months [18].Assessment of complications resulting from interventions during the study period.

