**Methods:**

The SCHOKE trial is a randomized, single-blind, parallel-group, sham-controlled trial designed to evaluate the effect of combined ESWL and endoscopic treatment for pain in patients with CP. In total, 106 adult patients with painful CP and pancreatic duct obstruction will be randomized to combined ESWL and subsequent endoscopic treatment or corresponding sham procedures. The primary outcome is pain relief during the 3-month postrandomization period as documented in a pain diary. Secondary outcomes include quality of life and functional scores, patient global impression of change, change in use of analgesics, frequency of hospitalization, and complications. Standard follow-up is at 3 and 6 months after randomization. In an experimental substudy, quantitative sensory testing obtained before and after intervention will be used to obtain information on central pain processing and to develop models for prediction of treatment outcome.

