### Randomization, blinding, and treatment allocation

Randomization is performed using an automatic assignment system that conceals allocation. Block randomization is employed with randomization of six patients per block to equal proportions for sham procedures or combined ESWL and endotherapy. No stratification of randomization based on demographic or clinical variables will be applied. The allocation sequence will be generated by a biostatistician who will not be involved in the administration of treatment or recording of data. Randomization of patients into the two groups will be done by a physician who will not have access to the clinical data of the patients.

The patients will be blinded to the treatment received. The patients in the sham procedure will be provided a superficial needle prick with a sterile needle to mimic epidural anesthesia. Then the ESWL instrument will be started so that the patients get an auditory perception that the treatment is being provided. The patient’s eyes will be covered, and if the patient wishes, he or she will be given light sedation. The operator cannot be blinded, owing to the nature of the study. However, the principal investigator and the statistician will be blinded to the treatment arms.

In case of an emergency that necessitates knowledge of the procedure allocation, the individual procedure assignment for each patient will be available. The codes will be available at the study center in sealed envelopes that are stored in a locked and secured area accessible only to those individuals authorized by the investigator. This procedure allows unblinding of individual subjects, without revealing codes of the entire study. The investigator will be able to determine which procedure a patient was given by opening the sealed envelope with the corresponding randomization number. The investigator must state the reason why the code was broken on the envelope and must date and sign it. At the end of the study, all sealed and unsealed envelopes must be accounted for.

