### Statistical analysis

The primary analysis of clinical endpoints will be by intention to treat, meaning that all randomized patients are included in their initially assigned study arm, regardless of adherence to the study protocol. Experimental endpoints will be evaluated by per-protocol analysis, meaning that only patients completing the experimental setup will be included. A repeated measures linear mixed effects model will be used for the primary analysis and will include terms for treatment group, assessment time point (week), and the interaction of treatment with assessment time point. Summary statistics of pain scores will be provided for the individual time points, and the difference in pain scores between groups after 3 months is considered the primary efficacy parameter. Subgroup and covariate analyses will be performed if applicable and in case differences in patient subgroups deemed clinically relevant are evident. Subsequent analyses directed at the secondary, experimental, and safety endpoints are analyzed using appropriate statistics, including mixed effect models, Fisher’s exact tests, and Student’s *t* tests or Wilcoxon rank-sum tests as appropriate. The predictive value of the QST profiles will be analyzed using logistic regression models.

We plan to conduct an interim analysis after approximately one-third of patients (*n* = 40) have been randomized and have completed 6 months of follow-up, using a two-sided significance test with the O’Brien–Fleming spending function and a type I error rate of 5%. An independent statistician, blinded to the treatment allocation, will perform the interim analysis. The statistician will report to an independent data and safety monitoring board (DSMB). The DSMB will have unblinded access to all data and will decide on the continuation of the trial and report to the internal review board of the Asian Institute of Gastroenterology. If there is a highly significant difference in improvement in pain in the treatment arm, then all subsequent patients will be subjected to this. The trial will not be stopped in case of futility, unless the DSMB advises otherwise during the course of safety monitoring.

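### The harm endpoint counts only complications judged to result from the interventions, so the comparison of harms is open to attribution that differs by arm

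*Protocol article*

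**What the plan says.** The last item under Secondary clinical endpoints is "Assessment of complications resulting from interventions during the study period". It is the only harm endpoint that the article names. Two other places describe the same outcome without a causal qualifier: the Methods part of the abstract ("change in use of analgesics, frequency of hospitalization, and complications") and the Fig. 1 legend ("anxiety and depression scores, patient global impression of change, and complications").

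The Sham treatment section gives control patients "sham ERCP with duodenal intubation of the endoscope and examination of the papillary area, but no pancreatic ductal intervention will be performed", and the lithotripter runs without contact with the body. On blinding, the article states "The operator cannot be blinded, owing to the nature of the study", but also that "the principal investigator and the statistician will be blinded to the treatment arms". It does not say who decides whether a complication was caused by a procedure.

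On analysis, the article states "Subsequent analyses directed at the secondary, experimental, and safety endpoints are analyzed using appropriate statistics", and Fisher's exact test is among the methods it lists. Hospital admissions and days in hospital are separate secondary endpoints, compared between arms with no attribution wording.

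**The concern.** A sham arm lets a trial measure excess harm without anyone having to judge cause, because the sham arm supplies the background rate. An endpoint that admits an event only after a causal judgement gives up part of that advantage.

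The risk is concrete here. Monitoring and safety names acute pancreatitis as a risk of ERCP and as something seen very infrequently after ESWL, so a flare in an actively treated patient is easily read as procedural. Anyone who knows that the duct was not touched has little reason to read a sham patient's flare that way. Flares unrelated to any procedure are foreseeable, since past acute pancreatitis is a baseline variable, and the window is the whole 6-month study period. If the filter works differently in the two arms, excess harm from active treatment is overstated. The endpoint would also show little of any reduction in later flares, because a flare months afterwards would seldom be attributed to a procedure in either arm.

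**Working it through.** **The plan's own figure.** The article gives no complication rate, flare rate or attribution rate, so there is nothing to reproduce for this endpoint. Its sample size figure (48 per group, 106 in total) concerns pain. The only input taken from it is the arm size: 106 / 2 = 53, from equal allocation.

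**Set-up.** Let r be the true 6-month flare rate, equal in both arms, and let q_A and q_S be the probabilities that a flare is attributed to the intervention in the active and sham arms. Each patient contributes at most one event. Then:

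- expected counted events: 53 × r × q_A in active and 53 × r × q_S in sham
- spurious risk difference: r × (q_A − q_S)
- chance of a nominally significant result: the sum of the two binomial probabilities over all pairs of counts for which two-sided Fisher's exact p < 0.05

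All values of r, q_A and q_S are assumptions.

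**Attribution 80% active v 20% sham**

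| r | Expected counts | Spurious difference | P(p < 0.05) |
|---|---|---|---|
| 5% | 2.1 v 0.5 | 0.05 × 0.6 = 3 points | 1.1% |
| 10% | 4.2 v 1.1 | 0.10 × 0.6 = 6 points | 10.9% |
| 20% | 8.5 v 2.1 | 0.20 × 0.6 = 12 points | 40.4% |
| 30% | 12.7 v 3.2 | 0.30 × 0.6 = 18 points | 67.2% |

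**Other attribution patterns, at r = 5%, 10%, 20% and 30%**

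- 80% v 40%: differences of 2, 4, 8 and 12 points; P(p < 0.05) of 0.7%, 4.7%, 15.1% and 28.1%.
- 80% v 0%: differences of 4, 8, 16 and 24 points; P(p < 0.05) of 1.9%, 24.8%, 87.1% and 99.4%.
- 80% v 80%, as a blinded assessor might produce: expected difference 0; P(p < 0.05) at most 3.0%.
- All flares counted in both arms: expected difference 0; P(p < 0.05) between 0.8% and 3.0%.

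With equal true rates, the distortion therefore depends wholly on q_A differing from q_S. At a 5% flare rate it rarely produces a significant test. At 20% and above it can do so often.

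**The case against.** A reader might infer that the harms comparison is biased as it stands and that sham flares are excluded by definition. The article supports neither. It does not give the operator the task of attributing cause, and the principal investigator is blinded to arm. The section headed Interventions covers both arms, and the sham arm has a needle prick, a duodenal endoscopy and sedation on request, so complications of sham procedures fall within the wording.

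A reader might also produce a dramatic example. With a 10% background rate and 5% added by ERCP, all-cause counts are 53 × 0.15 = 8.0 v 53 × 0.10 = 5.3, a difference of 5 points. If every active flare and no sham flare is attributed, the endpoint shows 8 v 0, a difference of 15 points. The arithmetic is right, but it needs 100% v 0% attribution sustained over 6 months, and nothing in the article indicates that.

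Other points on this side also stand. The item is worded as an assessment, whereas most of its neighbours are worded as differences between groups, and Fisher's test is a listed option for it, not a fixed one. Admissions and hospital days are compared whatever their cause, so flares leading to admission are still counted in both arms. Together with lost working days and pain scores, they would partly reflect any benefit on flares. Adverse event definitions, causality rules and the choice of assessor are commonly left to the full protocol, so their absence from an article is no finding.

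These points limit the concern without removing it. The causal filter is stated text, and more detail elsewhere would refine it, not lift it. Admissions do not identify acute pancreatitis, miss flares managed without admission, and can mix fewer pain admissions with more procedural ones. The unqualified wording in the abstract and the Fig. 1 legend means that one outcome is described in two ways that would yield different counts.

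**Conclusion.** The point holds as a weakness in how the endpoint is worded. The only named harm endpoint is filtered by causal attribution over 6 months, in a trial whose operator is unblinded and whose sham arm has no ductal intervention. It is open to differential attribution, and it does not give the all-cause rate of acute pancreatitis by arm. Actual bias is not demonstrated.

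The size depends on rates that the article does not give. With 53 per arm, equal true flare rates and 80% v 20% attribution, the spurious difference runs from 3 points at a 5% flare rate to 12 at 20%. With equal attribution it is 0. Severity is minor to moderate: this is one secondary endpoint, and the primary endpoint and sample size do not depend on it.

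**What to change.** Reword the endpoint as all adverse events and complications in both arms, from randomization to 6 months, regardless of attribution, with acute pancreatitis as a named component. Compare the arms on that count, for example by the proportion of patients with at least one event using Fisher's exact test, which is already listed. Keep procedure-attributed complications as a descriptive sub-listing, preferably judged by an assessor blinded to arm. Align the abstract, the Secondary clinical endpoints list and the Fig. 1 legend to the same definition.

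The cost is an endpoint amendment and a somewhat longer event form at contacts that already exist: the weekly calls during the diary period and the 3- and 6-month visits. More unrelated background events will be recorded. The sample size does not change. Recruitment had begun before the article appeared, so the change should be dated and made without sight of events by arm.
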